### Study population

Patients aged ≥18 years with ductal carcinoma in situ (DCIS) or biopsy-confirmed invasive T1–T3 breast cancer are eligible if clinically node-negative as confirmed by preoperative axillary ultrasound and if there is an indication for breast surgery with SLNB via axillary incision. Exclusion criteria include combined marking of the axillary node with a radioactive iodine seed procedure, known allergy to ICG, iodine or intravenous contrast agents, prior axillary lymph node dissection (ALND), hyperthyroidism or thyroid cancer, pregnancy or breast-feeding and absence of informed consent.

### Training

During Phase I, all participating sites receive a training programme, comprising an e-learning module, an in-person workshop and a train-the-trainer cascade. Training is evaluated through anonymous participant feedback, which is used to refine the e-learning module, in-person workshop and educational materials. Where feasible, all surgeons performing SLNB via axillary incision for breast cancer will participate directly. Alternatively, a train-the-trainer model may be applied, for example, in hospitals where SLNB is performed by a limited number of dedicated breast surgeons, who subsequently train colleagues locally. Before entering Phase II, each cluster must confirm site-level implementation readiness.

### Transition period

The fixed 6-month transition period is designed to accommodate the anticipated learning curve and is informed by prior research and implementation experience, including the coordinating hospital’s successful adoption of ICG as a single tracer following the INFLUENCE trial.^22^ When SLNB using ^99m^Tc-nanocolloid and blue dye was first implemented as an alternative to ALND, early reports described higher false-negative rates during the introductory phase.^42 43^ Subsequent studies showed that these learning-curve effects could be mitigated through structured training programmes, standardised protocols and on-site monitoring.^44^

In contrast, ICG-guided SLNB modifies an established surgical procedure rather than introducing a completely new one. Most procedural steps remain unchanged, and real-time fluorescence offers intuitive visualisation of the SLN, thereby limiting the need for extensive retraining. Empirical evidence on its learning curve remains limited, deriving mainly from two recent studies in which ICG was introduced alongside traditional tracers.^45 46^ Neither study evaluated transition to ICG as a single tracer, and both also included SLNB performed through the mastectomy incision, for which dedicated evidence remains limited. These studies therefore provide indirect, but reassuring, insights into the learning curve of ICG-guided SLNB via axillary incision.

A 6-month transition period was selected to provide sufficient opportunity for surgeons across participating hospitals to safely gain experience with ICG while retaining ^99m^Tc-nanocolloid as a within-patient control. This duration accommodates variation in surgical volume, prior experience with fluorescence-guided surgery and team composition, ranging from dedicated breast surgery teams to mixed surgical services. It also allows sufficient case accrual to achieve performance stabilisation before reliance on ICG alone. A fixed transition period promotes progression across sites, while three-monthly evaluations enable timely identification of sites requiring additional training, mentoring or support.

### ICG administration

ICG is reconstituted with sterile water for injection to obtain a 2.5 mg/mL (0.25% or 3.2 mM) solution. A total dose of 5 mg (2 mL) is injected intra- and subdermally into two to four periareolar sites after induction of general anaesthesia but before disinfection and sterile draping. The dose and injection technique are based on the INFLUENCE trial, which demonstrated non-inferior SLN detection compared with ^99m^Tc-nanocolloid using this approach in the Dutch clinical context. This dosing regimen falls within the recommended range and maximum daily dose specified in the Summary of Product Characteristics. Periareolar intra- and subdermal injections were selected for their reproducibility and suitability for palpable and non-palpable tumours.

### SLNB per study phase

#### Phase I (pre-implementation period)

SLNB is performed using ^99m^Tc-nanocolloid, according to standard clinical practice (figure 3). At the Nuclear Medicine Department, ^99m^Tc-nanocolloid is injected the morning of surgery (70 MBq) or the preceding day (150 MBq), followed by lymphoscintigraphy and skin marking of the SLN location. Intraoperatively, the SLN is identified using a handheld gamma probe providing auditory feedback. The lymph node (LN) with the highest counts per 10 seconds is considered the SLN; if two LNs demonstrate equal counts, both are classified as SLNs.

**Figure 3 F3:**
[figure not shown]
Sentinel lymph node biopsy procedure per study phase. ICG, indocyanine green; SLNB, sentinel lymph node biopsy; ^99m^Tc, radioisotope technetium-99m.

#### Phase II (transition period)

During the transition period, both ICG and ^99m^Tc-nanocolloid are administered. Preoperative preparation at the Nuclear Medicine Department mirrors Phase I, with the exception that skin markings are omitted and surgeons are blinded to lymphoscintigraphy results. Intraoperatively, the SLNB is guided primarily by ICG, with ^99m^Tc-nanocolloid serving as a within-patient control.

ICG is administered as described in the ICG administration section. A caudal axillary incision is made 5–30 min after injection, and SLNB is performed before breast tumour resection. Lymphatic channels may be clipped to prevent ICG leakage. The SLN is defined as the LN with the highest fluorescent signal and is excised first. The axilla is subsequently inspected for residual fluorescent LNs; if present, up to two additional LNs may be excised. All excised LNs are assessed ex vivo for ^99m^Tc uptake. The axilla is then explored for residual ^99m^Tc activity using the gamma probe, supplemented by inspection and palpation. Additional LNs are excised in accordance with the predefined limit of two.

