### Statistical analysis

#### Quantitative analysis

Baseline characteristics and quantitative outcome variables will be summarised using descriptive statistics. Continuous variables will be reported as means with SD or as median with IQR, based on distribution. Distributional assumptions will be assessed by visual inspection of histograms, and homogeneity of variances will be evaluated using Levene’s test. Dichotomous and categorical data will be presented as frequencies with percentages.

Where applicable, comparisons will be performed using the Student’s t-test for normally distributed continuous variables, the Mann-Whitney U-test for non-normally distributed continuous variables, and the χ^2^ or Fisher’s exact test for categorical variables.

Penetration, the primary implementation outcome, will be reported as a proportion with corresponding 95% CIs, without formal between-group comparisons. Adoption and fidelity outcomes will be reported descriptively as proportions with accompanying counts. Safety outcomes will be reported descriptively as proportions of patients experiencing ICG-related (serious) adverse events, with corresponding 95% CIs.

Effectiveness outcomes will be analysed according to study phase. A pre–post implementation analysis will compare observational cohorts of Phase I (^99m^Tc-nanocolloid) and Phase III (ICG). For these phases, effectiveness outcomes will be reported with 95% CIs and include per-case SLN detection rates, per-node SLN detection by tracer, number of excised LNs per procedure, detection time, SLNB duration and pathological outcomes of excised SLNs. Phase II will be analysed separately using a within-patient approach. In this phase, per-node SLN detection will be reported separately for ICG and ^99m^Tc-nanocolloid, and tracer concordance will be evaluated by quantifying agreement at the LN level. In addition, a paired within-patient comparison of per-case SLN identification by ICG versus ^99m^Tc-nanocolloid will be performed. Phase II outcomes will be reported descriptively with corresponding 95% CIs, using paired statistical methods where appropriate.

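### In Phase II, if the limit of two additional nodes is shared between the ICG and gamma steps, hot nodes that ICG missed can stay in place and drop out of the node-level comparison

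*Protocol article*

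**What the plan says.** The section on Phase II under SLNB per study phase fixes the order of the procedure:

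1. "The SLN is defined as the LN with the highest fluorescent signal and is excised first".
2. "The axilla is subsequently inspected for residual fluorescent LNs; if present, up to two additional LNs may be excised".
3. "All excised LNs are assessed ex vivo for ^99m^Tc uptake".
4. "The axilla is then explored for residual ^99m^Tc activity using the gamma probe, supplemented by inspection and palpation".
5. "Additional LNs are excised in accordance with the predefined limit of two".

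The same section gives the radioisotope its role: "Intraoperatively, the SLNB is guided primarily by ICG, with ^99m^Tc-nanocolloid serving as a within-patient control".

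Under Quantitative analysis, Phase II is analysed in three ways: per-node detection for each tracer, a paired per-case comparison, and concordance, where "tracer concordance will be evaluated by quantifying agreement at the LN level". Table 1 lists the concordance outcome as concordance of SLNs. The article defines the radioisotope SLN only under Phase I, as the node with the highest count (both nodes if equal), and does not repeat this for Phase II.

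**The concern.** The limit is introduced in the ICG step and invoked again in the gamma step. The article does not say whether the second mention is the same allowance or a new one. If it is the same, fluorescent nodes always draw on it before hot nodes can, and a patient with three fluorescent nodes has no room left for a hot node that did not fluoresce.

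Such a node is exactly what a within-patient control is there to reveal. If 99mTc status is known only for nodes that were removed, it appears neither as a node ICG missed nor as a discordant pair. ICG per-node detection and concordance would then look better than they were. A larger sample would not remove this bias, and no analysis plan can recover activity that was never written down.

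**Working it through.** **The plan's own figures.** The article gives no figure for this point. Its only precision figures, under Sample size, reproduce with n = 280: 1.96 × √(0.50 × 0.50 / 280) = 5.9 points (stated as roughly 6) and 1.96 × √(0.95 × 0.05 / 280) = 2.6 points (stated as 2–3). The point does not depend on them.

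**What happens to a fourth node.** Take a patient in whom three fluorescent nodes have been excised, so the ICG step has used its two additional places. A fourth node D remains.

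- D is hot and not fluorescent. Shared limit: D stays and is missing from a table of excised nodes. Separate limit: D is excised and scored 99mTc-positive, ICG-negative. The loss favours ICG.
- D is fluorescent and cold. The ICG step cannot take it under either reading, so an ICG-positive, 99mTc-negative node is lost. This favours 99mTc.
- D is fluorescent and hot. Shared limit: a concordant node is lost.

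Losses can therefore run both ways. They are not balanced, because the ICG step draws on the allowance first.

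**Case level.** A limit used up in the ICG step means that fluorescent nodes were found, so ICG already has its detection and no ICG failure can be hidden. What can be lost is a 99mTc detection, when none of the excised fluorescent nodes is hot and the hot node stays in place.

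**Size, on assumptions.**

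- Phase II patients: each cluster spends a fixed 6 of 18 months in Phase II (Study design; Timeline and cluster transition). With even accrual, 850 × 6/18 = 283. The total of 850 is from Sample size.
- Assumed, not in the documents: 1.5 hot nodes per patient, so 283 × 1.5 = 424.5 hot nodes; a share h of patients with one hot node that ICG missed; a share q of patients at the limit after the ICG step, independent of h.

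Missed nodes M = 283h. Unobserved nodes U = qM. True ICG detection of hot nodes = 1 − M/424.5. Observed detection = 1 − (M − U)/(424.5 − U).

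| h | M | q | U | True | Observed |
|---|---|---|---|---|---|
| 2% | 5.7 | 10% | 0.6 | 98.7% | 98.8% |
| 2% | 5.7 | 30% | 1.7 | 98.7% | 99.1% |
| 5% | 14.2 | 10% | 1.4 | 96.7% | 97.0% |
| 5% | 14.2 | 30% | 4.2 | 96.7% | 97.6% |
| 10% | 28.3 | 10% | 2.8 | 93.3% | 94.0% |
| 10% | 28.3 | 30% | 8.5 | 93.3% | 95.2% |

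At h = 5% and q = 30%, U = 0.30 × 14.15 = 4.245, and observed detection is 1 − 9.905/420.255 = 97.6%. The upward shift at h = 5% is 0.3 to 1.0 points. For scale, the binomial half-width on 424.5 nodes at 96.7% is 1.96 × √(0.967 × 0.033 / 424.5), about 1.7 points, ignoring clustering of nodes within patients.

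**The case against.** The strongest reply is that the problem exists only if the limit is shared, and the material that might settle this is not visible. Figure 3 shows the procedure by phase but is not reproduced, and the full protocol and forms are not at hand. The gamma search is described, so its result may well be recorded; an article commonly leaves out form fields. Nor does the article say outright that agreement is computed on excised nodes only. This stands as a limit on the point, which is therefore conditional. It does not remove it: the sentence on the gamma step refers back to a limit already set, only one has been set, and no rule is given for activity left in place.

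The shift is also small. Under the central assumptions it lies inside the sampling error of the estimate, and the outcomes concerned are secondary and reported descriptively. That stands too.

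A reader might go further in four ways that the documents do not support:

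- That discordant nodes vanish in one direction only. Fluorescent cold nodes beyond the limit can also be left.
- That every patient at the limit has a truncated control. With 10–30% at the limit that would be 28–85 of 283 patients, but control data are lost only where a residual hot node also exists.
- That every residual hot spot is an ICG miss. It may be a fluorescent node that the limit left behind.
- That Phase II is the evidence on which the move to ICG alone rests. Phase II has a fixed length, no concordance threshold for entering Phase III is stated, and the Introduction and the implementation section rest the change on an earlier non-inferiority trial and the literature. The Discussion gives the within-patient comparison a supporting role.

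**Conclusion.** The point holds in conditional form. On the natural reading of the Phase II text the limit is shared, and hot nodes that ICG missed can then be left in place and go uncounted in per-node detection and node-level concordance. The net effect tends to favour ICG. At case level only a 99mTc detection can be lost.

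With 283 Phase II patients, 1.5 hot nodes each, 5% of patients with an ICG-missed hot node and 10–30% at the limit, about 1.4–4.3 nodes go unobserved, and apparent ICG detection of hot nodes rises from 96.7% to 97.0–97.6%. All but the patient count are assumptions made for illustration, and the patient count itself assumes even accrual. If the gamma step has its own allowance of two, the loss is confined to patients with more than two residual hot nodes.

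The change should be made: it is cheap, and the missing information cannot be reconstructed later.

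**What to change.** - **Text.** The clinical team should reconcile the two sentences, so that it is clear whether nodes found by the gamma probe fall under the limit of the ICG step. No limit is proposed here.
- **Case report form.** After the ICG step and before any further excision, record whether residual gamma activity is present, the number of hot spots, whether each is fluorescent, and whether it was then excised.
- **Node-level analyses.** Count a residual hot spot as 99mTc-positive and ICG-missed only if it is not fluorescent. For concordance of SLNs, apply the plan's own SLN definition, stating whether the Phase I rule for the radioisotope SLN carries over to Phase II.
- **Per-case comparison.** Credit 99mTc with a detection where a hot node was identified but not excised.
- **Reporting.** Give the number of patients who reached the limit in the ICG step, with a sensitivity analysis that excludes them.

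The cost is a few form fields on a search that is already part of the procedure, plus some analysis wording. The trial began on 18 April 2025, so procedures already done may lack these fields; their number should be reported.

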#### Phase III (post-implementation period)

SLNB is performed using ICG as a single tracer, following the same technique as described for Phase II but without concurrent use of ^99m^Tc-nanocolloid as a within-patient control. This approach eliminates the need for a preoperative visit to the Nuclear Medicine Department.

### An integrated implementation approach

The INFINITE trial employs an integrated implementation approach that combines a complementary process model, determinant framework and evaluation framework, consistent with Nilsen’s taxonomy.^47^ The implementation process is guided by the Grol and Wensing Model of Implementation of Change.^48^ Barriers and facilitators to implementation are identified using the updated Consolidated Framework for Implementation Research (CFIR).^49^ Implementation outcomes, intervention outcomes and patient-reported experience are structured using the Outcomes for Implementation Research framework by Proctor *et al.*^50^ Together, these frameworks support a theory-based, systematic and reproducible implementation strategy that may inform similar implementation efforts in other settings.

The Grol and Wensing process model outlines seven, often iterative, steps to support systematic change (figure 4).^48^ Steps 1–3 were completed prior to trial initiation. In Step 1, the proposed change was to replace ^99m^Tc-nanocolloid with ICG as the tracer for SLNB via axillary incision in breast cancer. This proposal was supported by evidence from the INFLUENCE trial and a growing body of literature demonstrating non-inferiority of ICG-guided SLNB, together with several advantages compared with conventional tracers, which informed Step 2 (analysis of performance).^2022 23 26^,^33^ In Step 3, a problem analysis was conducted using the Value Proposition Canvas to systematically map the limitations of ^99m^Tc-nanocolloid and identify the unmet needs of patients and healthcare providers.

**Figure 4 F4:**
[figure not shown]
Integrated implementation approach. Combining the Grol and Wensing Model of Implementation of Change, Proctor’s outcomes framework, the Consolidated Framework for Implementation Research (CFIR) and the Expert Recommendations for Implementing Change (ERIC) with the CFIR-ERIC matching tool^48^,^51^. CASH, Cursorisch onderwijs AIOS Heelkunde (Dutch national surgical training programme for residents); CFIR, Consolidated Framework for Implementation Research; ERIC, Expert Recommendations for Implementing Change; ICG, indocyanine green; SLN, sentinel lymph node; ^99m^Tc, radioisotope technetium-99m; ZonMw, Netherlands Organisation for Health Research and Development.

In Step 4, six initial implementation strategies were selected. Their selection was informed by the Step 3 problem analysis, complemented by determinants from the SLNB and ICG-fluorescence literature and input from the multidisciplinary project team. The strategies were operationalised using the Expert Recommendations for Implementing Change (ERIC) project and Netherlands Organisation for Health Research and Development (ZonMw) guidelines (figure 4).^51^ Patient-centred strategies involve engagement of the patient panel throughout the study, including the development and evaluation of knowledge products. Informative strategies comprise disseminating information at professional meetings, through scientific associations and in peer-reviewed journals. Support-building strategies include organising in-person workshops aimed at strengthening clinical support and stakeholder engagement, which also serve as an educational strategy by facilitating knowledge transfer and skill development. Educational strategies are further supported by embedding an ICG-guided SLNB module in the Dutch national surgical training programme for surgical residents (Cursorisch onderwijs AIOS Heelkunde, CASH). Facilitative strategies aim to support consideration of ICG-guided SLNB for inclusion in national breast cancer guidelines and are supported by ZonMw project funding. Product-oriented strategies involve identifying stakeholder needs regarding key implementation tools and developing these materials accordingly (eg, the concept implementation guide, medical protocol and patient information). These strategies may be adapted during the trial as part of ongoing iterative evaluation cycles.

Step 5 comprises the small-scale introduction of ICG during the stepped-wedge trial in motivated clinical teams, accompanied by the development and testing of a uniform medical protocol and an implementation guide. Step 6 evaluates the extent to which ICG replaces ^99m^Tc-nanocolloid for SLNB in participating sites, with penetration as the trial’s primary outcome. Step 7 entails iterative, 3-month evaluation cycles embedded in the trial. Barriers and facilitators will be identified using the updated CFIR across five domains: innovation, outer setting, inner setting, individuals and implementation process.^49^ This is predominantly a project-based activity supporting iterative optimisation, with the CFIR-ERIC matching tool used to refine implementation strategies where appropriate.^51^ The recurring evaluation cycles also allow timely identification of sites that require additional support. One CFIR-based assessment is conducted as a formal research component. This is embedded within the trial’s mixed-methods design and comprises brief open-text questions in the healthcare provider questionnaire administered in the third month of Phase III.^49^ These responses contextualise the quantitative survey outcomes.

### Outcomes and outcome measures

Following the framework of Proctor *et al,*^50^ outcomes are categorised into three domains: implementation outcomes (penetration, adoption, fidelity, appropriateness, feasibility and acceptability), intervention outcomes (effectiveness, safety and costs) and patient-reported experience (patient satisfaction). Table 1 provides an overview of all outcomes, definitions, outcome measures and data sources or instruments.

**Table 1 T1:** Overview of implementation, intervention and patient-reported experience outcomes with corresponding definitions, outcome measures and data sources

Implementation outcomes	Definition	Outcome measure	Data source/instrument
Adoption	Intention, initial decision or action to try or employ ICG fluorescence	Proportion of hospitals performing SLNB with ICG only (Phase III) Proportion of surgeons performing SLNB with ICG only (Phase III)	Quantitative: hospital administrative data
Penetration	Integration of a practice within a service setting and its subsystems	Proportion of SLNB procedures performed with ICG only relative to all SLNBs in the target population (Phase III)	Quantitative: hospital administrative data
Fidelity	Degree to which ICG fluorescence is implemented as intended	Proportion of SLNB procedures conducted according to protocol (Phase III) Number, type and reasons for protocol deviations related to ICG preparation, storage and administration (Phase III)	Intraoperative healthcare provider questionnaire with embedded open-text fields (Phase III)
Appropriateness	Healthcare providers perceived fit, usefulness and relevance of ICG fluorescence for identifying the SLN	Perceived relevance Perceived strength of evidence Reliability of ICG fluorescence Patient-specific suitability Overall level of appropriateness	Healthcare provider questionnaire (REDCap) with embedded open-text fields (Phase III)
Feasibility	Extent to which ICG fluorescence can be successfully used within a given setting	Site readiness (availability of fluorescence imaging equipment) Ease of learning Experience with dual-tracer SLNB prior to transitioning to ICG only Confidence in transitioning to ICG only Suitability for routine clinical practice Team attitude and motivation Collaboration with nuclear medicine Overall level of feasibility	Healthcare provider questionnaire (REDCap) with embedded open-text fields (Phase III)
Acceptability	Extent to which healthcare providers perceive ICG fluorescence to be agreeable, palatable or satisfactory	Perceived relative advantage Ease of use, complexity and patient-friendliness Overall level of acceptability Preference for ICG vs ^99m^Tc-nanocolloid and underlying reason Willingness for sustained use Likelihood of recommending ICG fluorescence to colleagues	Healthcare provider questionnaire (REDCap) with embedded open-text fields (Phase III)

Intervention outcomes	Definition	Outcome measure	Data source/instrument
Effectiveness		Lymph node yield per SLNB procedure (total number of excised lymph nodes, including SLNs and non-SLNs) (all phases) Per-case SLN detection rate, defined as the proportion of SLNB procedures in which ≥1 SLN is identified by the assigned tracer (Phases I and III) Within-patient per-case SLN detection comparing ICG and ^99m^Tc-nanocolloid (Phase II) Per-node SLN detection by tracer, reported separately for ICG and ^99m^Tc-nanocolloid (all phases) Tracer concordance of SLNs (Phase II) Detection time, defined as time from axillary skin incision to excision of the first SLN (all phases) Total SLNB duration, defined as time from axillary skin incision to axillary wound closure (all phases) Pathological classification of excised SLNs (benign, isolated tumour cells, micrometastases, macrometastases), reported per node and per patient and stratified by tracer and study phase (all phases)	Quantitative: perioperative data collected by healthcare providers during SLNB and supplemented with patient file data, entered into REDCap case report forms
Safety		(Serious) adverse events potentially related to ICG administration (Phases II and III)	Quantitative: postoperative REDCap case report forms using patient file data
Costs		Cost overview analysis (healthcare provider perspective): comparison of per-patient and in-hospital costs of SLNBs using ICG vs ^99m^Tc-nanocolloid Budget impact analysis (national scale-up): projected economic impact on the Dutch healthcare system over a 5-year period through phased implementation of ICG-guided SLNB Patient-incurred costs related to SLNB, including travel, sick leave and childcare needs (Phases I and III)	Quantitative: hospital administrative data, financial data and national costing guidelines; ZonMw Budget Impact Analysis tool with sensitivity analysis; phase-specific postoperative patient questionnaire (REDCap)

Patient-reported experience	Definition	Outcome measure	Data source/instrument
Satisfaction	Satisfaction with various aspects of ICG fluorescence: content, complexity, comfort, delivery and credibility	Patients perceived satisfaction with SLNB experience using ^99m^Tc-nanocolloid, dual-tracer SLNB and ICG only	Phase-specific postoperative patient questionnaire (REDCap), with embedded open-text fields

Definitions of implementation, intervention and patient-reported experience outcomes are based on Proctor *et al.*^50^

ICG, indocyanine green; 99mTc, radioisotope technetium-99m; REDCap, research electronic data capture; SLN, sentinel lymph node; SLNB, sentinel lymph node biopsy; ZonMw, Netherlands Organisation for Health Research and Development.

These outcome domains are interrelated; the quality of implementation may influence both intervention performance and patient experience, which in turn may affect sustained uptake. Quantitative data alone are not sufficient to understand the contextual factors underlying these relationships.^52^ Therefore, the trial primarily follows a quantitative design with an embedded mixed-methods component, limited to the questionnaire-based outcomes assessing appropriateness, feasibility, acceptability and patient satisfaction. These questionnaires mainly include closed-ended items, supplemented by brief open-ended questions that allow respondents to elaborate on their responses, consistent with a concurrent one-phase mixed-methods design.^53^ The qualitative data serve a complementary and explanatory role that may contextualise the quantitative findings. The study will be reported in accordance with the Good Reporting of A Mixed Methods Study (GRAMMS) and Standards for Reporting Implementation Studies (StaRI) guidelines.^54 55^

